## Rationale for Study Design and Methodological Choices in the CHAMBER

### Target Population

The aim is to collect a study population as homogeneous as possible in terms of obstructive symptoms. Children under 6 months of age primarily suffer from bronchiolitis, which has been shown to respond poorly to bronchodilator therapy. Bronchiolitis refers to inflammation of the terminal bronchioles in infants. In children over 4 years of age, obstruction is more frequently associated with asthma that typically requires regular medication. Therefore, the study will recruit children aged 6 months to 4 years, focusing primarily on treating symptoms triggered by viral infections in this age group.

### Sample Size

Based on previous studies [12],[13] and clinical experience, we estimate that the average RDAI score for children presenting to the emergency department is 11 and that this score decreases to approximately 5 after treatment. The primary outcome is the difference in post-treatment RDAI score between the groups. A difference of at least 2 points is considered clinically meaningful. The sample size is calculated to detect a minimum 2-point difference in final RDAI score (measured at the time of treatment outcome decision) with 90% statistical power ( $\beta$ -error 10%) and 95% confidence ( $\alpha$ -error 5%). The between-group difference in RDAI scores will be analyzed using a t-test, and the standard deviation is assumed to be 2.5 based on earlier studies. Thus, 33 children per group are needed for the final analysis. We anticipate that approximately 15% of enrolled children will be excluded from the analysis due to protocol deviations (e.g., adverse effects, insufficient efficacy, or poor treatment adherence). Therefore, 40 children will be recruited per group, for a total of 80 participants.

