| RDAI-scores
<del>SaO2</del> | SaO2 (Amended in 13.1.2025. Decision made to have only one primary outcome that was the base of the sample size calculation. SaO2 was moved from Main outcomes to Secondary outcomes)
Change in respiratory rate (difference before and after medication)
Heart rate (difference before and after medication)
<del>Need for oral prednisolone</del> (Amended in 25.2.2021. The proportion of children receiving oral corticosteroids will be reported as baseline characteristic instead of outcome because they were often given before and/or during the intervention)
Number (proportion) of patients admitted to the hospital
Parents' assessment of treatment success (Table 4)
Healthcare personnel's assessment of treatment success (Table 4)
Proportion of patients requiring a fourth dose of medication
<del>Number of return visits</del> (Amended in 25.2.2021. Outcome removed because it is not feasible to collect the data reliably in all the centers) |

**Table 4.** Assessment of treatment adherence and perceived effectiveness of inhalation therapy using a structured scoring system

|                                  | Points |   |   |   |   |   |
|----------------------------------|--------|---|---|---|---|---|
|                                  | 0      | 1 | 2 | 3 | 4 | 5 |
| Evaluated by the nurse           | 0      | 1 | 2 | 3 | 4 | 5 |
| Evaluated by the parent/guardian | 0      | 1 | 2 | 3 | 4 | 5 |

0 = medication administration failed; 1 = child is crying continuously; 2 = child is crying, screaming, or resisting, but not continuously; 3 = child shows some resistance to medication administration but does not cry or scream; 4 = good cooperation, but the child appears uncomfortable; 5 = good cooperation and calm breathing throughout medication administration. Adapted from Minh et al. [11]. If the nurse rates the medication administration as 0–2 points, the same dose is repeated once.

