### **Treatment of the Enrolled Child in the Emergency Department**

The study physician assesses the severity of the child's respiratory distress and records the RDAI score as well as other clinical variables listed in Table 3 on the study form. The child receives salbutamol via either the BH or OD spacer, with a dose based on weight (0.6 mg or 0.8 mg, corresponding to 6 or 8 actuations), up to four times at 20-minute intervals (Figure 4).

The study physician reassesses the clinical variables (Table 3) before treatment and again 20 minutes after the first two doses. If the child still requires bronchodilator treatment, up to two additional doses (0.6 or 0.8 mg, depending on weight) are administered. The physician again assesses breathing effort 20 minutes after the third and, if given, the fourth dose, and then makes the decision regarding further treatment (discharge or hospitalization, Figure 4). Otherwise, the follow-up and care of study participants will proceed in the outpatient clinic according to standard clinical practice.

In children under the age of 3, the spacer is used with a face mask; in older children, it may be used without a mask when appropriate. Salbutamol is administered one puff at a time into the spacer, and after each actuation, the child should take at least five breaths through the device. If the child strongly resists medication administration or is crying (Table 4), the same dose should be reattempted once the child has calmed down.

If a child enrolled in the Chamber study is discharged from the outpatient clinic, they will be given the spacer used during the study free of charge, along with written instructions for continued care. If the child is admitted to the hospital, treatment will continue on the ward using the same spacer device that was used in the emergency department.

**Figure 3.** Median dose of salbutamol delivered from spacer devices (% of nominal dose) and range measured using a filter (in vitro filter dose), when used without a mask (no mask) or with a mask (with mask). Measurements were performed using devices from three different production batches (LOT).

[figure not shown]

RR, respiratory rate. Vt, tidal volume.

LOT, production batch. P-values shown above the bars refer to differences with or without a mask, based on the Mann-Whitney U test.

P-values below the graph refer to differences between devices from different production batches, based on the Kruskal-Wallis test.

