## Statistical analysis

All statistical analyses will be conducted in the intention-to-treat population based on predefined outcome measures, comparing children treated with each of the two valved holding chambers. Continuous variables with normal distribution will be analyzed using the unpaired *t*-test, and non-normally distributed data using the Mann–Whitney *U* test. Differences in proportions will be assessed with the standard normal deviate (*Z*) test for proportions. Results will be presented as proportions, risk differences, risk ratios, and numbers needed to treat (NNT), each with corresponding 95% confidence intervals (CIs).

*Amended in 25.2.2021, new analysis added: A sensitivity analysis will be performed excluding children with poor cooperation, defined as a mean cooperation score below 4.*

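### The primary RDAI comparison ignores the baseline RDAI recorded in every child, which costs precision and leaves chance imbalance in severity in the estimate

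*Protocol*

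**What the plan says.** The Sample Size section of the protocol defines the endpoint: "The primary outcome is the difference in post-treatment RDAI score between the groups". It then names the test: "The between-group difference in RDAI scores will be analyzed using a t-test". The Statistical analysis section applies the same approach to every continuous outcome: "Continuous variables with normal distribution will be analyzed using the unpaired" *t*-test, with the Mann–Whitney *U* test when the data are not normal. Neither test uses a baseline value. The only further analysis is a sensitivity analysis that leaves out children who cooperated poorly.

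Baseline RDAI is available for everyone. A score of at least 6 is an entry criterion (Study Population). The section on treatment in the emergency department says that, at the initial assessment, the study physician "records the RDAI score as well as other clinical variables listed in Table 3 on the study form".

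Table 3 uses a different convention for two secondary outcomes. Respiratory rate and heart rate are before-to-after differences, for example "Heart rate (difference before and after medication".

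**The concern.** Baseline and final RDAI are the same instrument, scored in the same child during one visit. Entry scores can run from 6 to the scale maximum of 17, with an expected mean of 11, so starting severity is an obvious candidate predictor of the final score. The design does not balance it: the permuted blocks are set up per centre, with no stratification by severity. A difference in starting severity that arises by chance therefore enters the primary estimate, scaled by the slope of final on baseline score. The confidence interval is also wider than the collected data allow.

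The change scores for respiratory rate and heart rate err the other way. They subtract the whole baseline value, which over-corrects whenever the slope is below 1. With at most 40 children per arm, neither convention is the efficient one.

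**Working it through.** **Inputs from the protocol (Sample Size).** Difference 2 points ("The sample size is calculated to detect a minimum 2-point difference in final RDAI score"); SD 2.5 ("the standard deviation is assumed to be 2.5 based on earlier studies"); power 90% ("with 90% statistical power"); α 5%, taken as two-sided; 33 per arm analysed, 40 per arm recruited.

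**Assumptions, because the protocol gives no figure.** The baseline–final correlation r, shown over a range; a baseline SD of 2.5, equal to the final SD, so that the slope of final on baseline equals r.

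**1. The plan's own figure.** n per arm = 2 × [2.5 × (1.960 + 1.282) / 2]² = 32.8, rounded up to 33. The stated number reproduces. With 33 per arm, power is 90.1% by the normal approximation and 89.3% by the noncentral t distribution. The noncentral t is used below.

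**2. Precision with baseline adjustment.** Residual SD = 2.5 × √(1 − r²). Approximate 95% CI half-width at 33 per arm = 1.96 × SD × √(2/33).

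| r | Residual SD | Half-width, 33 per arm | Power, 33 per arm | Power, 40 per arm |
|---|---|---|---|---|
| 0 (planned test) | 2.50 | 1.21 | 89.3% | 94.2% |
| 0.2 | 2.45 | 1.18 | 90.4% | 95.0% |
| 0.3 | 2.38 | 1.15 | 91.8% | 95.9% |
| 0.4 | 2.29 | 1.11 | 93.7% | 97.1% |
| 0.5 | 2.17 | 1.04 | 95.9% | 98.3% |
| 0.6 | 2.00 | 0.97 | 97.9% | 99.3% |

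The adjusted rows allow one degree of freedom for the baseline covariate. Adding centre (four sites, so three more) lowers power by less than 0.1 percentage point.

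**3. Chance imbalance.** SE of the difference in mean baseline RDAI = 2.5 × √(2/n): 0.62 points at 33 per arm and 0.56 at 40. The shift in the unadjusted estimate is slope × imbalance.
- A 1-SE imbalance with slope 0.5: 0.5 × 0.62 = 0.31 points, or 15% of the 2-point target.
- A 1.96-SE imbalance at 33 per arm (1.21 points): 0.36, 0.60 and 0.84 points at slopes 0.3, 0.5 and 0.7. The middle value is 30% of the target.

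**4. Change scores against baseline adjustment.** With equal SDs, the variance ratio is 2(1 − r)/(1 − r²) = 2/(1 + r): 1.54, 1.33 and 1.18 at r = 0.3, 0.5 and 0.7. Moving RDAI to a change score would therefore not solve the problem. The SD of the change is 2.5 × √(2(1 − r)), which is 2.96 at r = 0.3 and falls to 2.5 only at r = 0.5.

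**The case against.** The strongest reply is that nothing here is invalid. Under randomisation the t-test is unbiased and keeps its type I error, its standard error already allows for chance imbalance, and the trial is powered for it. All of that stands, and it makes this a point about efficiency and about the estimate given the imbalance that actually occurs.

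The size of the gain is also uncertain. The entry threshold and the aim of a homogeneous population narrow the baseline range. Extra doses for children who still need treatment may further weaken the link between baseline and final score. At r = 0.1 the power at 33 per arm would be 89.5% against 89.3%, which is almost no gain. If all 80 children are analysed, as the intention-to-treat statement implies, the unadjusted test already has 94.2% power, and r = 0.3 adds less than two percentage points. These limits are fair. However, 33 per arm is the protocol's own analysis size, and a gain, even if smaller, remains at 40.

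The Mann–Whitney route is a real gap for any replacement. RDAI is bounded at 0 and saturation has a ceiling, so a linear model must come with a rule for poorly behaved residuals.

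Finally, covariate adjustment is often left to an SAP. Here the protocol itself names the primary test, so an SAP that adjusted would depart from it.

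**Conclusion.** The concern holds. The protocol fixes an unadjusted comparison of final RDAI although a baseline RDAI exists for every child and severity is not balanced by design. The cost is modest if r is about 0.2 to 0.3 (one to three percentage points of power at 33 per arm) and substantial if r is 0.5 or more (95.9% against 89.3% at r = 0.5, with the CI half-width falling from 1.21 to 1.04 points). Ordinary chance imbalance could move the estimate by about 0.3 points, and an imbalance at the edge of the 95% range by about 0.6, both with slope 0.5. These sizes rest on the assumed r, on a baseline SD of 2.5 and on equal SDs before and after treatment. The direction does not depend on the exact values, provided baseline predicts the final score at all. This is a change that should be made; it does not put the trial's validity in doubt.

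**What to change.** Amend the Sample Size and Statistical analysis sections as follows.

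- **Primary analysis:** a linear model of post-treatment RDAI on device, with baseline RDAI and centre as covariates, reporting the adjusted mean difference with its 95% CI.
- **Secondary continuous outcomes:** the same form for SaO2, respiratory rate and heart rate, that is, the post-treatment value adjusted for its own baseline in place of a raw difference.
- **Non-normality:** state in advance what replaces the switch to Mann–Whitney, for example robust standard errors in the same model, with the rank test as supportive.
- **Sensitivity analysis:** keep the unadjusted t-test.

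The sample size can stay as it is. The cost is wording only, with no new data and at most four degrees of freedom. Timing matters: recruitment was expected to start in spring 2019 and the latest amendment shown is dated 13.1.2025. The change must be dated and documented before any comparison of the coded groups has been seen, so that the adjustment cannot look like a response to an observed imbalance. If that is no longer possible, report the adjusted model as a supportive analysis and say when it was chosen.

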### Study Population

The study will include a total of 80 children aged 6 months to 4 years who are diagnosed with moderate or severe bronchial obstruction (RDAI score  $\geq 6$ , Table 2), and whose guardians have provided written, informed consent. The severity of respiratory distress is assessed using a previously published Respiratory Distress Assessment Instrument (RDAI) [12, 13].

Children will be excluded from the study at the emergency department if they meet any of the following criteria:

1. Require immediate inpatient care
2. Have an oxygen saturation ( $SpO_2$ ) below 85% upon arrival
3. Are diagnosed with bacterial or viral pneumonia
4. Show inspiratory crackles (suggestive of bronchiolitis in infants)
5. Are diagnosed with acute laryngitis (croup)
6. Are suspected to have or are confirmed to have a foreign body in the airway
7. Have liver or kidney dysfunction
8. Are immunocompromised or have another chronic condition deemed exclusionary by the attending physician
9. Have bronchopulmonary dysplasia due to prematurity
10. Are currently using a long-acting beta-agonist (LABA)
11. Have previously participated in this study
12. Refuse to take medication via spacer
13. Have participated in another clinical trial within the 30 days prior to enrollment

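### The Sample Size section plans to exclude about 15% of children from the analysis, for reasons that include insufficient efficacy, which contradicts the protocol's intention-to-treat rule

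*Protocol*

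**What the plan says.** The Sample Size section of the protocol plans for a 2-point between-group difference in final RDAI score, an SD of 2.5, 90% power and a 5% alpha error. This gives 33 children per group for the final analysis. It then anticipates that about 15% of enrolled children "will be excluded from the analysis due to protocol deviations (e.g., adverse effects, insufficient efficacy, or poor treatment adherence", and on that ground recruits 40 per group, 80 in total.

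The Statistical analysis section states: "All statistical analyses will be conducted in the intention-to-treat population based on predefined outcome measures". An amendment of 25.2.2021 in the same section adds a sensitivity analysis that leaves out children whose mean cooperation score is below 4.

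Neither section refers to the other. The protocol does not define its intention-to-treat population or say which statement prevails.

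**The concern.** The two sections give different answers to the question of who enters the primary comparison. Both are current text.

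The exclusion sentence does not describe ordinary dropout. It speaks of exclusion, not of missing data or withdrawal, and its examples all arise after randomisation. They also overlap with what the trial measures: symptom relief, treatment acceptance and adverse effects are all listed under Study Objectives. Insufficient efficacy is, in substance, a poor result on the primary outcome. These children need not be missing either. The final RDAI is taken at the time of the discharge-or-admission decision, so a child who responds poorly should still have a score.

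The trial's premise is that one device delivers less drug. If that is so, that arm will produce more children with insufficient efficacy, and removing them improves the apparent result of the worse device. Hospital admission, a secondary outcome, would be affected in the same way. Exclusion for poor adherence could also rest on ratings by the nurse and parent, who are not blinded to the device.

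A null result after such exclusions could not be told apart from an artefact. A positive result could be challenged over the choice of analysis population.

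**Working it through.** **Inputs from the Sample Size section.** Difference: "The sample size is calculated to detect a minimum 2-point difference in final RDAI score". SD: "the standard deviation is assumed to be 2.5 based on earlier studies". Power: "with 90% statistical power". Alpha is 0.05 ("95% confidence"). Test: "The between-group difference in RDAI scores will be analyzed using a t-test". Sidedness is not stated; two-sided is assumed, because a one-sided test would need only 27 per group.

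**Step 1: reproduce the plan's figures.**

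n per group = 2 × [SD × (z₀.₉₇₅ + z₀.₉₀) / Δ]² = 2 × [2.5 × (1.960 + 1.282) / 2]² = 32.84, rounded up to 33. The t-test version gives 33.8, that is 34.

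Inflation: 33 / 0.85 = 38.8 (39), or 34 / 0.85 = 40.0. The stated 33 and 40 reproduce. The arithmetic is sound; the fault lies in what the 15% stands for.

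**Step 2: what the exclusions would do if applied.** The protocol gives no split of the 15% by reason, so everything in this step is an assumption. Final scores are taken as normal with means 5 and 7 and SD 2.5, with 40 recruited per arm.

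*Extreme case: exclusion removes exactly the worst final scores.* For a cut-off c, the mean of the retained children is μ − SD × φ(b)/Φ(b), with b = (c − μ)/SD. For 15% removed overall, c = 8.80:

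- Better arm: b = 1.52, retained mean 5 − 2.5 × 0.134 = 4.66.
- Worse arm: b = 0.72, retained mean 7 − 2.5 × 0.403 = 5.99.
- Difference: 5.99 − 4.66 = 1.33.

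| Worst scores removed (pooled) | Removed, better arm | Removed, worse arm | Difference | Power (normal approx.) |
|---|---|---|---|---|
| 5% | 1.5% | 8.5% | 1.67 | 89% |
| 10% | 3.7% | 16.3% | 1.48 | 84% |
| 15% | 6.4% | 23.6% | 1.33 | 77% |

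*Milder case: 15% are excluded, but exclusion is only correlated with a poor final score (simulation).*

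| Correlation | Removed, better arm | Removed, worse arm | Difference |
|---|---|---|---|
| 0.3 | 12.2% | 17.8% | 1.94 |
| 0.5 | 10.4% | 19.6% | 1.82 |
| 0.8 | 7.9% | 22.1% | 1.56 |

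*Adverse-effect exclusions falling on the best responders* (correlation 0.3 to 0.5) give 1.94 to 1.83.

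The loss across these scenarios runs from about 0.06 to 0.67 of the 2 points.

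**Step 3: power if nobody is excluded for these reasons.** With a 2-point difference and SD 2.5, t-test power is 90.2% at 34 per group and 94.2% at 40.

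Those figures assume the full effect survives when poor adherers are retained. If 15% of children gain nothing from the better device, the difference is 0.85 × 2 = 1.7. Power at 40 per group is then Φ(1.7/2.5 × √(40/2) − 1.96) = Φ(3.04 − 1.96) = Φ(1.08), about 86%.

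**The case against.** The strongest reply is that the 15% sentence is only a recruitment allowance, whereas the Statistical analysis section is the operative rule and covers every analysis. The 2021 amendment supports this: excluding poor cooperators in a sensitivity analysis makes sense only if the main analysis keeps them. On that reading no bias arises. This stands as far as it goes: the contradiction is certain, but the bias is conditional on the planning sentence being carried out. It does not remove the contradiction. The sentence says children will be excluded from the analysis, the recruitment target rests on it, and it still lists poor adherence after the amendment dealt with cooperation differently.

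Three stronger readings are tempting, and the documents do not support them.

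- A reader might infer that the trial's result will be biased toward zero. That does not follow. Under the intention-to-treat rule there is no such bias, and exclusions unrelated to outcome would cause none. Excluding poor adherers could even raise the difference, since it removes children in whom the device has little chance to matter. The toward-zero direction belongs to exclusion for insufficient efficacy and, in the scenarios above, for adverse effects in the best responders.
- A reader might take 1.33 points as the expected result. It is the extreme case, in which every exclusion falls on the worst final scores.
- A reader might see the same problem in the entry criterion "Refuse to take medication via spacer", if it were applied once the device is known. The section on Recruitment and Randomization fixes the order: exclusion criteria are checked first, and the envelope is opened only after written consent.

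**Conclusion.** The point holds as an internal contradiction about who is analysed. The Sample Size section should not stand as written beside the intention-to-treat commitment.

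The consequence is conditional and its size cannot be fixed from the protocol. If the exclusions were applied for reasons linked to poor response, a true 2-point difference would be estimated at between about 1.94 (weak link) and 1.33 (extreme case), with power down to about 77% in the latter. These figures rest on normal scores, SD 2.5 and assumed links between exclusion and outcome.

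The sample size itself is adequate and reproduces.

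**What to change.** In the Sample Size section, replace the exclusion sentence with wording to this effect: all randomised children are analysed in the group to which they were allocated; adverse effects, insufficient efficacy and poor adherence are not grounds for exclusion from the primary analysis; and the 15% is an allowance for children without a final RDAI score. Keep the cooperation-based exclusion as a sensitivity analysis only, as the Statistical analysis section already has it.

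If power is restated, give about 90% with 34 per group and about 94% with all 40 under the protocol's own assumptions, and add that it is lower if retained poor adherers dilute the effect (about 86% at 1.7 points).

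The cost is a change of wording, to be made before the group codes are broken. It needs no further patients and no new data.
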